## Methods

### Design and setting

The primary objective of this study is to assess whether tailored motivational messages supporting smoking cessation—as selected by a health recommender system and delivered by mobile phones to patients—contribute to higher smoking cessation rates.

Secondary objectives include: (1) comparing smoking cessation rates to other user metrics and technical aspects of the system; (2) investigating the relationship between usage of the app used in the 3M4Chan intervention [35] and users’ opinions of messages; and (3) determining if a relation exists between the users’ physical activity levels and their mobile app usage, and their smoking cessation rates.

Both the primary objective and the secondary objectives are common for the clinical and public pilots, although their methodologies and assessments do not completely coincide.

The present document shows the protocol version 1.0.4, 30 May 2018. Major protocol amendments, if any, will be handled by the Taipei Medical University informing any involved stakeholder, and updating the ClinicalTrials.gov registry diligently. Table 1 describes the clincal and public pilot. We followed the Standard Protocol Items: Recommendations for Intervention trials (SPIRIT) guidelines while writing this protocol manuscript (see Additional file 1).

**Table 1 Tab1:** Description of the clinical and public pilot

Name of the pilot	Number of patients	Groups	Treatment	Data to be assessed
Clinical pilot (RCT; 100 patients)	50	Control	Usual care (behavioral therapy and pharmacological treatment)	Smoking cessation rate (clinically validated)
	50	Intervention	Usual care + 3M4Chan app (advanced tailored messages)	Smoking cessation rate (clinically validated)
				Recommender system
				User engagement
				Physical activity
Public pilot (RCT; 1000 patients)	500	Control	m-health (basic tailored messages)	Smoking cessation rate (self-reported)
				Recommender system
				User engagement
				Physical activity
	500	Intervention	m-health (advanced tailored messages)	Smoking cessation rate (self-reported)
				Recommender system
				User engagement
				Physical activity

*RCT* randomized controlled trial

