### Measures: baseline and outcome and process measures

The clinical pilot and public pilot are different interventions with shared metrics and also exclusive ones to each case. The primary outcome, the smoking cessation rates, will be measured at the 60, 120, and 180-day follow-up time points, using the urinary cotinine and expired carbon monoxide levels in the clinical pilot case, and the self-reported questionnaires in the public pilot case. To assess the secondary outcomes, different metrics are required. Table 2 includes information about how they will be calculated, to which other metrics they will be compared, and to which pilot they are related.

**Table 2 Tab2:** Description of metrics to assess the primary and secondary outcome

Metric	Calculation	Comparisons	Pilot	Related secondary outcome
Primary outcome				
Smoking cessation rate	Total number of people who relapsed / total number of people in the group at 60 days, 120 days, and 180 days of their quitting date	• User engagement at an individual level • User engagement at an aggregated level • User mobile app usage • User quitting attempts • User lifestyle feedback • Physical activity	• Clinical • Public	System influence on smoking cessation and app influence on users physical activity levels
Secondary outcomes				
User engagement at an individual level	Messages read by the user / total number of messages sent to the user	• Smoking cessation rate	• Public • Clinical	System influence on smoking cessation
Engagement at an aggregated level	Mobile application rolling retention, session length distribution, session frequency, sessions per user, return rate	• Smoking cessation rate	• Public • Clinical	System influence on. smoking cessation.
User quitting attempts	Number and date of quitting attempts	• Smoking cessation rate	• Public • Clinical	System influence on smoking cessation
User app behavior	Time spent per app section	• User message ratings • User satisfaction with messages	• Public • Clinical	App usage. and opinions on messages the users received
User satisfaction with messages	Satisfaction questionnaire	• User mobile app usage • Mobile app behavior • User message ratings	• Clinical	App usage and opinions on messages the users received
User message ratings	Users’ votes for each message on a 5-star scale	• User app behavior	• Public • Clinical	App usage and opinions on messages the users received

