### Statistical analysis

In the clinical pilot, patients will be classified as either smokers or non-smokers according to their positive or negative values in the urine test and the expired CO tests (PiCO values between 0 and 6 will be considered non-smokers) at each follow-up visit. In case of discrepancy between tests, we will consider the patient as a smoker. We will perform repeated analysis of variance (ANOVA), and provide *p* values, to compare the number of non-smokers in the intervention versus control group at 2 months, 4 months and 6 months of their quitting day.

In the public pilot, users will be considered to be non-smokers according to their self-reported answer to the question: “Are you still resisting the temptation or have you smoked? Please, be honest.” We will perform repeated ANOVA, and provide *p* values, to compare the number of non-smokers in the intervention versus control group every 2 weeks.

For secondary outcomes, the numerical variables (user engagement at aggregated level, user mobile app usage, user quitting attempt, user app behavior, and user lifestyle feedback EuroQoL 5 dimensions 5 levels questionnaire (EQ-5D-5 L) and Short Form 36-item Health Survey (SF-36), and physical activity) will be assessed with *T* tests and variance ANOVA tests. Categorical variables (user engagement at individual level, user satisfaction with messages, user message ratings, and lifestyle answers to the International Physical Activity Questionnaire (IPAQ)) will be assessed with chi-square tests. In addition, we intend to study the combination of all metrics with a linear regression analysis, and the Kaplan-Meier method to analyze the overall survival rate (non-smokers). All tests will be two-tailed and with a significance level set at 0.05. All analyses will be done according the intention-to-treat principle, and using the SPSS software version 25. Missing data will be calculated with the last observation carried forward.

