### Sample size and power calculations

Calculations regarding the needed number of participants to measure the primary outcome – smoking cessation rates – have been done to ensure the statistical significance of the results.

For the clinical pilot, accepting an alpha risk of 0.05 and a beta risk of 0.2 in a two-sided test, 45 subjects will be necessary in both the first group and second groups in order to find a statistically significant proportion difference, which is expected to be 0.2 and 0.5 in the first and second groups, respectively.

For the public pilot, accepting an alpha risk of 0.05 and a beta risk of 0.2 in a two-sided test, 489 subjects are necessary in first group and 489 in the second to find as statistically significant a proportion difference, expected to be of 0.07 in group 1 and 0.14 in group 2.

A dropout rate of 15 and 20% is anticipated for the clinical and public pilot, respectively. Although other studies using computer-tailored interventions have reported higher dropout rates, this study will consider participants who do not return for the consultation at month 6 to be failure cases. Consequently, the anticipated dropout rates include only those who withdraw for reasons other than relapse.

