### Materials

The clinical pilot will make use of all the materials normally used to treat patients at the smoking cessation units at Taipei Welcome Clinic and Taipei Medical University Hospital.

Carbon monoxide levels will be tested using a PiCO Smokerlyzer CO-oximeter; a value range of 0–6 will be considered normal for a non-smoker. Similarly, a Safecare Biotech COT Rapid Test device, which contains line indicators for positive and negative test results, will be used to measure urinary cotinine levels.

Several smoking cessation medications will be used during the trial: Nicotinell TTS 20 and TTS 30 patches, Nicotinell 2-mg chewing gum and 10-mg inhalers, Buporin 150-mg sustained-release tablets, and Champix 0.5-mg and 1-mg tablets. The dosage and duration of each medication will be prescribed by the physician, and the patients will be charged NT$200 per consultation.

In addition, our specially designed mobile app will be used to deliver motivational health messages. Figure 3 shows its interface in both English and Mandarin. The app has been programmed in Android’s native language. It uses Mirth Connect as its communication channel [39], Firebase for platform notifications, and PostgreSQL as its database management system.

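### Clinical pilot: the rule that any disagreement between urine cotinine and expired CO means smoker misclassifies tobacco-abstinent patients who are using a nicotine patch, gum or inhaler at the visit

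*Protocol article*

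**What the plan says.** The section on measures sets the primary outcome of the clinical pilot at 60, 120 and 180 days, "using the urinary cotinine and expired carbon monoxide levels in the clinical pilot case". The Statistical analysis section classifies each patient "according to their positive or negative values in the urine test and the expired CO tests", with CO from 0 to 6 counted as non-smoking. It resolves disagreement in one sentence: "In case of discrepancy between tests, we will consider the patient as a smoker". No exception is stated.

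The Materials section describes the urine device as one "which contains line indicators for positive and negative test results, will be used to measure urinary cotinine levels", so the result is read as yes or no. The same section lists the medications used during the trial. They include "Nicotinell TTS 20 and TTS 30 patches, Nicotinell 2-mg chewing gum and 10-mg inhalers", together with Buporin and Champix. It adds: "The dosage and duration of each medication will be prescribed by the physician". Table 1 (Design and setting) gives pharmacological treatment as part of usual care, and both arms receive usual care.

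Nowhere does the article exempt users of nicotine products from the cotinine criterion, let CO decide for them, use a tobacco-specific marker, or place the end of nicotine replacement before a visit.

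**The concern.** The strip detects exposure to nicotine, while the endpoint is meant to measure smoking. The two differ in patients who have quit with the help of a nicotine product. For them the pattern of low CO with positive cotinine is what successful treatment can look like, and the rule turns it into a failure.

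The endpoint then depends partly on which medication was prescribed and for how long: of two abstinent patients, one on a patch and one on Champix, only the first can be scored as a smoker for this reason. At stake are the level of the cessation rates, the size of the difference between arms and the power. If nicotine-product use differs between the arms, the comparison itself is also at stake. A false smoker result at day 60 can enter the repeated analysis and the Kaplan-Meier analysis, and last observation carried forward can extend it if later visits are missed.

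This is a rule that the article states and fixes, not a detail left to another document.

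**Working it through.** **Step 1. Follow the rule for one patient.** Take a patient who has not smoked and is wearing a patch at the visit.
- CO is in the range 0–6, so the CO test says non-smoker.
- The strip detects cotinine from the patch, so the urine test says smoker.
- The tests disagree, so the patient is scored as a smoker.

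The device gives no level that could separate replacement from smoking. For a patient on Buporin or Champix alone, the medicine causes no such disagreement.

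**Step 2. Reproduce the plan's sample size.** Inputs from Sample size and power calculations: two-sided alpha 0.05, beta 0.2, rates 0.2 and 0.5. So d = 0.30 and the mean rate is 0.35.
- Uncorrected: n₀ = [1.96·√(2·0.35·0.65) + 0.8416·√(0.2·0.8 + 0.5·0.5)]² / 0.30² = (1.322 + 0.539)² / 0.09 = 38.5, rounded up to 39.
- Continuity-corrected: n = (n₀/4)·[1 + √(1 + 4/(n₀·d))]² = 9.62 × 2.160² = 44.9, rounded up to 45.

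The plan's 45 per group is reproduced with the continuity correction, so that basis is used below. The figure itself is not in dispute.

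**Step 3. Put the misclassification in.** Let f be the share of true abstainers whose strip is positive because of a nicotine product. The documents do not give f; the range 0 to 0.5 is an assumption. Observed rate = true rate × (1 − f). If f is equal in both arms, the observed difference is 0.30 × (1 − f).

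Power at n = 50 per arm is Φ[(d − 1/n − 1.96·se₀)/se₁], with se₀ = √(2·p̄·(1−p̄)/n) and se₁ = √((p₁(1−p₁) + p₂(1−p₂))/n).

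For f = 0: (0.30 − 0.02 − 1.96 × 0.0954)/0.0906 = 1.03, so power is 0.85.

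| f (both arms) | Observed rates | Difference | n per arm needed | Power at 50 per arm |
|---|---|---|---|---|
| 0 | 0.20 / 0.50 | 0.30 | 45 | 0.85 |
| 0.1 | 0.18 / 0.45 | 0.27 | 53 | 0.78 |
| 0.2 | 0.16 / 0.40 | 0.24 | 62 | 0.69 |
| 0.3 | 0.14 / 0.35 | 0.21 | 74 | 0.60 |
| 0.5 | 0.10 / 0.25 | 0.15 | 113 | 0.40 |

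Power is 0.81 at f = 0.05 and 0.78 at f = 0.1, so it drops below the planned 0.80 between these values. The table counts all 50 patients per arm; the anticipated 15% dropout is not deducted. It refers to two proportions at a single visit, as the plan's own calculation does.

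**Step 4. Let f differ by arm.**
- Control 0.1, intervention 0.3: 0.18 against 0.35, difference 0.17.
- Control 0.3, intervention 0.1: 0.14 against 0.45, difference 0.31.

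The true difference is 0.30 in both cases. With no true effect and a rate of 0.20 in each arm, the first pattern gives 0.18 against 0.14, a spurious difference of 0.04 against the app; the second gives the same 0.04 in its favour.

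**The case against.** The strongest reply is that this is a strict, pre-specified rule applied identically in both arms. If nicotine-product use is equal, a true null stays null and the ratio of rates stays at 0.50/0.20 = 2.5 for every f. That is right: under equal use the cost is a smaller absolute difference and lower power, not a false positive result. It does not hold when use differs by arm, as step 4 shows.

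Second, the size is unknown. The article gives neither the share of patients on nicotine products nor the strip's cut-off. Replacement may have ended for many patients by day 180. This stands. But the article fixes no duration, and days 60 and 120 are primary time points too.

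Third, 0.20 and 0.50 are described only as expected rates. If they already mean rates as measured under this rule, the loss of power in the table is zero. This also stands, so the table is an illustration.

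A reader might infer that the rule works against the app, because app users adhere better to treatment and so more of them test positive. The documents do not support that direction. The message topics listed under the procedure for generating texts do not include medication adherence, both arms get the same usual care, and care providers are told to treat the groups equally. Nor do the documents support saying that every patient prescribed nicotine replacement is misclassified: only tobacco-abstinent patients with replacement nicotine still detectable at a visit are affected.

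**Conclusion.** The concern holds as a defect of the classification rule in the clinical pilot. Applied as written, the rule scores a tobacco-abstinent patient with a positive strip from a nicotine patch, gum or inhaler as a smoker in the primary endpoint. The public pilot relies on self-report and is not affected.

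That the rule misclassifies such patients follows from the stated rule, the listed medications and the fact that cotinine comes from nicotine of any source. How much it matters does not follow from the documents. Assuming that 0.20 and 0.50 are true abstinence rates and f is equal in both arms, a share of 0.1 is already enough to bring 50 per arm below the planned power. With unequal shares the estimate can be too small or too large, and the article gives no ground for expecting one direction.

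**What to change.** Change the classification rule only:

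1. At each of the 60-, 120- and 180-day visits, record in both arms whether the patient is currently using a nicotine-containing product (yes/no). Treatment adherence is already reviewed at every consultation, so this adds one data field.
2. For patients recorded as users, treat cotinine as uninformative and classify by expired CO (0–6) alone.
3. For all other patients, keep the present requirement that both tests be negative.
4. Report two sensitivity analyses: the present strict rule, and CO alone for everyone.

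Self-report is better left out of the rule. Daily cigarette use is not listed for the third and fourth consultations, and patients know whether they have the app, so answers could differ by arm.

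Two downsides should be stated in the plan. CO has a shorter detection window than cotinine, so some recent smoking among users will be missed. The test standard also comes to depend on medication use after randomisation; if use differs by arm, more patients in one arm are judged by the more lenient standard. The analysis with CO alone for everyone checks this.

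Recruitment is under way according to Trial status. For visits already held, the field would have to be filled from treatment records as far as they allow. No change to treatment is involved.

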## Abstract

**Background:**

Smoking cessation is the most common preventative for an array of diseases, including lung cancer and chronic obstructive pulmonary disease. Although there are many efforts advocating for smoking cessation, smoking is still highly prevalent. For instance, in the USA in 2015, 50% of all smokers attempted to quit smoking, and only 5–7% of them succeeded – with slight deviation depending on external assistance. Previous studies show that computer-tailored messages which support smoking abstinence are effective. The combination of health recommender systems and behavioral-change theories is becoming increasingly popular in computer-tailoring. The objective of this study is to evaluate patients’s smoking cessation rates by means of two randomized controlled trials using computer-tailored motivational messages. A group of 100 patients will be recruited in medical centers in Taiwan (50 patients in the intervention group, and 50 patients in the control group), and a group of 1000 patients will be recruited on-line (500 patients in the intervention group, and 500 patients in the control group). The collected data will be made available to the public in an open-source data portal.

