### Recruitment procedure

The participants in this study can be divided into two groups: those who participate in the clinical pilot and those who take part in the public pilot. Participants in the clinical pilot will be recruited from smoking cessation units at Taipei Wellcome Clinic and the Taipei Medical University Hospital in Taiwan between 1 September 2017 and 31 July 2018. They will be asked by a nurse or researcher, whether they want to be part of the study in the waiting room before their first visit to the smoking cessation unit. They will be handed written information about the reasoning of the study, and further, they have to sign an informed consent to participate (Additional file 2). The public pilot will be open to any smoker who is willing to quit. In both pilots, each participant must own an Android mobile phone, and accept the terms and conditions of the services provided by the 3M4Chan app. The participants for the public pilot will be recruited online among all the Taiwanese population between 1 September 2017 and 31 July 2018. They will be invited to join the study by downloading the app. These invitations will be done with targeted ads on Facebook and Google, as well as with retargeting banners, which have previously been proven to be successful [36]. In addition, posters and informative leaflets will be distributed at the above-mentioned smoking cessation units and at Health Promotion Administration centers in Taiwan to attract candidates in non-digital environments. A total of four posters, 200 leaflets, and 400 business card-sized advertisements will be printed to disseminate information about the app.

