**Fig. 3 Fig3:**
[figure not shown]
Screenshots of the app (English and Mandarin versions) showing different sections

A nurse will provide patients with instructions for downloading and using the app. Questions related to the patient’s basic demographic information and an extended profile (including social influences, plan of action, skills, attitudes, and self-efficacy with regard to smoking) will be assessed in the app.

The data obtained from the database will be analyzed in a comma-separated value (CSV) format using SPSS software.

Users’ physical activity data will be collected using their mobile phones. The mobile app will use GoogleFit [40] to track daily physical activity. These data will be available to users through the GoogleFit app but not displayed within the 3M4Chan app, as it will be utilized for research purposes only.

Patients will be followed up after 60, 120, and 180 days of their initial consultation with a variance margin of 5 days. In the initial consultation, the patient will be assessed in the smoking cessation unit after they have been referred from either the pneumology unit or another clinical department. Smoking-related symptoms, treatment adherence, daily cigarette use, and possible adverse events will be discussed and exhaled carbon monoxide, urinary cotinine, and other clinical information, such as weight and height, will be assessed. Quality of life (EQ-5D-5 L, IPAQ, and SF-36) questionnaires will also be collected. The patient will be instructed on relaxation techniques and on tips to avoid smoking.

During the second consultation, physicians will gather patient information on smoking-related symptoms, treatment adherence, daily cigarette use, possible adverse events, exhaled carbon monoxide and urinary cotinine levels, and other clinical information. Coaching for relapse prevention will be performed.

At the third consultation, information about smoking-related symptoms, treatment adherence, possible adverse events, exhaled carbon monoxide and urinary cotinine levels, and other clinical information will again be collected. New relaxation techniques will be explained if the previously taught techniques have not been effective. Techniques for relapse prevention will be reviewed. It will also be collected the users’ physical and psychological health state, their exhaled carbon monoxide levels, the results from a urinary cotinine test, and will be asked clinical information such as weight and height.

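### The clinical pilot's primary comparison names no baseline covariate although daily cigarette use and exhaled CO are recorded at entry, so it may give up a little precision

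*Protocol article*

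**What the plan says.** Under Statistical analysis, clinical-pilot patients are classed as smokers or non-smokers at each follow-up visit from the urine test and expired CO; if the two disagree, the patient counts as a smoker. The arms are then compared by repeated ANOVA "to compare the number of non-smokers in the intervention versus control group at 2 months, 4 months and 6 months of their quitting day". The section also fixes the significance level, intention-to-treat, the missing-data rule and the software. It names no covariate for this comparison.

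The only regression mentioned is a supplementary linear regression on the study's metrics taken together. Tables 2 and 3, which define those metrics, do not list baseline CO or baseline cigarettes per day as adjustment variables.

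The Materials section describes the initial consultation, where "daily cigarette use, and possible adverse events will be discussed and exhaled carbon monoxide, urinary cotinine, and other clinical information" are among the items covered. Patients are "recruited from smoking cessation units at Taipei Wellcome Clinic and the Taipei Medical University Hospital", so recruiting unit is known for everyone. The Randomization section describes computer-generated random numbers and mentions no stratification.

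The Sample size section treats the comparison as two plain proportions. It sets the error rates by "accepting an alpha risk of 0.05 and a beta risk of 0.2 in a two-sided test" and from these concludes that "45 subjects will be necessary in both the first group and second groups", for a proportion "which is expected to be 0.2 and 0.5 in the first and second groups, respectively". Planned enrolment is "50 patients in the intervention group, and 50 patients in the control group".

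**The concern.** If heavier smokers at entry are less likely to be abstinent later, part of the outcome variation within each arm can be explained by data already in hand. Leaving it unexplained makes the estimated difference less precise than it could be. In a trial of about 100 patients, even a modest gain is worth having when it needs no extra patient, visit or test.

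At stake are a few points of power and a somewhat narrower confidence interval. The validity of the comparison is not at stake. Timing matters: covariates fixed before outcomes are examined are credible, while covariates chosen afterwards invite selective reporting.

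**Working it through.** **Inputs from the protocol.** Proportions 0.2 and 0.5, two-sided alpha 0.05, power 0.80, 45 per arm required, 50 per arm planned. On dropout: "A dropout rate of 15 and 20% is anticipated for the clinical and public pilot, respectively". That gives 50 × 0.85 = 42.5, about 43 per arm. If month-6 non-returners count as failures, as the Sample size section says, up to 50 per arm can be analysed.

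**Input not in the protocol.** The within-arm correlation ρ between baseline smoking and later abstinence is an assumption, shown from 0 to 0.4.

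**1. Reproduce the plan's figure.**

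n₀ = [1.96·√(2·0.35·0.65) + 0.8416·√(0.2·0.8 + 0.5·0.5)]² / 0.3² = 38.48

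With continuity correction: n = (n₀/4)·[1 + √(1 + 4/(n₀·0.3))]² = 44.90, so 45 per arm. The stated figure is reproduced exactly, as an unadjusted comparison of two proportions.

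**2. Power with adjustment, by formula.** Adjustment multiplies the variance by (1 − ρ²):

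Power = Φ( 0.3 / √[(0.41/n)(1 − ρ²)] − 1.96 ), where 0.41 = 0.16 + 0.25.

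Example, n = 43: √(0.41/43) = 0.0976, so unadjusted power is Φ(3.07 − 1.96) = 86.7%. At ρ = 0.3 the standard error becomes 0.0976·√0.91 = 0.0931, giving Φ(3.22 − 1.96) = 89.6%.

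| n per arm | unadjusted | ρ 0.2 | ρ 0.3 | ρ 0.4 |
|---|---|---|---|---|
| 43 | 86.7% | 88.0% (+1.3) | 89.6% (+2.9) | 91.8% (+5.1) |
| 50 | 91.2% | 92.2% (+1.0) | 93.5% (+2.3) | 95.1% (+3.9) |

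The continuity-corrected formula behind the plan's 45 starts lower: 77.9% at 43 and 84.8% at 50. With n replaced by n/(1 − ρ²), ρ = 0.2, 0.3 and 0.4 give 79.9%, 82.3% and 85.7% at 43, and 86.4%, 88.4% and 91.1% at 50. These gains are a little larger, partly because the substitution also shrinks the correction term. The simulation below is the better guide.

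**3. Check by simulation.** Logistic outcome model with one baseline covariate, arms set to 0.2 and 0.5, linear model with and without the covariate, 6,000 trials per cell. Here ρ is the square root of the within-arm R² (for example √0.081 = 0.28).

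| ρ in the two arms | odds ratio per SD | n = 43 | n = 50 |
|---|---|---|---|
| 0 | 1.00 | 85.8% → 85.0% | 89.7% → 89.7% |
| 0.19 to 0.24 | 1.65 | 86.0% → 87.0% | 89.0% → 90.8% |
| 0.28 to 0.33 | 2.12 | 84.8% → 87.4% | 89.2% → 92.1% |
| 0.37 to 0.42 | 2.72 | 85.2% → 89.6% | 89.8% → 94.2% |

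A separate simulation at 45 per arm with HC3 standard errors gave 85.9% → 88.0% (ρ about 0.29), 85.4% → 90.6% (ρ about 0.38) and 86.0% → 84.9% (ρ 0). Adjusted type I error stayed between 3.7% and 5.3%.

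**4. Cost if the covariates are useless.** With one, about 1 point or less (rows with ρ = 0 above). With three (two continuous, one binary; HC3, 20,000 trials), power fell from 84.7% to 81.7% at 43, from 86.1% to 84.0% at 45, and from 89.1% to 87.8% at 50. That is a loss of 1.3 to 3.0 points.

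All these figures are for a comparison at one time point, as in the plan's own sample size calculation, and not for the repeated ANOVA.

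**The case against.** The strongest objection is that the absence of adjustment is read from silence. The article does not say the comparison is unadjusted, and an analysis plan that is not shown may list covariates. This stands as a caution. However, the article specifies its analysis closely and sizes the trial without covariates, so suggesting a better version of the stated method is fair.

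Four stronger readings are tempting, and the documents support none of them.

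- **A large, certain loss of power.** At ρ = 0.5 the variance falls by a quarter, equivalent to one third more patients (1/0.75 = 1.33). Nothing in the protocol supports that value. Even ρ of about 0.4 needs an odds ratio near 2.7 per standard deviation of baseline smoking.
- **CO must predict strongly because the outcome is built on it.** Everyone enters as a current smoker, so the binary outcome has no baseline variation, and CO is only one of the two tests that define it. The entry criterion of smoking at least monthly is a floor; the actual spread of smoking intensity is not documented.
- **Chance imbalance biases the result.** Randomisation keeps the unadjusted test valid, and its standard error already allows for chance imbalance. Adjustment improves precision only.
- **The sample size is wrong.** The figure of 45 is reproduced exactly. Without the continuity correction, unadjusted power at 43 to 50 per arm is already above 80%.

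It is also true that with weak predictors the cost of three covariates is about as large as the gain. That argues for one or two covariates, not for none.

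**Conclusion.** The point holds as a low-severity efficiency improvement. The stated primary comparison uses no baseline covariate, two plausible ones are collected, and at 43 to 50 per arm adjusting may recover some precision. The gain is roughly 0 to 2 points of power at ρ = 0.2, 2 to 4 at 0.3 and 4 to 6 at 0.4, and nil or slightly negative if baseline smoking does not predict abstinence. This rests on the plan's 0.2 versus 0.5, two-sided 0.05, a single-time-point comparison and an assumed ρ. It concerns the clinical pilot only: with 489 to 500 per arm in the public pilot, the same step gains under 4 points even at ρ = 0.5.

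**What to change.** In Statistical analysis, state that the clinical pilot's between-arm comparison of non-smoker status is adjusted for baseline daily cigarette use, baseline exhaled CO or both, with recruiting unit optional. Use a model suited to a binary outcome, applied at the plan's stated time points. One option is logistic regression, with the adjusted risk difference obtained by standardisation and a robust standard error. Report the adjusted risk difference and show the unadjusted difference alongside. Name the covariates before outcome data are examined. If an analysis plan already lists covariates, bring this section into line with it.

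The cost is a sentence or two of text and a little more analysis, with no new patients, visits or tests. The downside is about 1 point of power or less with one covariate that proves non-predictive, and about 1 to 3 points with three, so the list should stay short.
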